## Abstract

**Background:**

Post-dural puncture headache (PDPH) is one of the most common complications of neuraxial anaesthesia. It limits patients’ general activity and increases the length of hospital stays and the use of care. It is particularly disabling during the postpartum period, when mothers have to take care of their child. Epidural blood patch is the standard treatment for PDPH. However, it is an invasive procedure that may result in rare but serious complications. Recent evidence has suggested that adrenocorticotropic hormone (ACTH) is effective in the management of PDPH. The aim of this study is to assess the efficacy and safety of tetracosactide (Synacthen®), a synthetic analogue of ACTH, for PDPH treatment in patients who receive neuraxial anaesthesia during labour.

**Methods:**

This randomised, double-blind, placebo-controlled, parallel-arm trial, is performed in two French university hospitals. Eligible patients are those suffering from postpartum PDPH, who are randomised to receive either 1 mg of tetracosactide intravenously over 20 min or to 0.9% saline (placebo). The primary endpoint is the rate of epidural blood patch within a 15-day follow-up period. Headache duration, pain intensity, reduction of general activity, increase in length of hospital stay, adverse events, analgesic use (type and duration) and number of blood patches per patient in each group are recorded.

**Discussion:**

We expect a decrease in the use of epidural blood patch in those receiving tetracosactide, thus indicating a decrease in PDPH symptoms in these patients. This will define the therapeutic success of tetracosactide and the possibility to use this treatment as a non-invasive alternative to blood patch for PDPH treatment.

**Trial registration:**

*Primary Registry*

ClinicalTrials.gov Protocol Registration and Results System

Date of Registration 24 June 2016

Unique Protocol ID 69HCL15_0429

*Secondary IDs*

EudraCT Number 2015–003357-17

ClinicalTrials.gov ID NCT02813655

ANSM 160214A-31

**Protocol version**

V4 28/09/2018

## Background

Epidural analgesia is the most effective method to control pain during labour and is frequently used in France (77% of vaginal deliveries in 2010) [1]. For caesarean sections, artificial deliveries, or uterine revisions, spinal anaesthesia is preferred to general anaesthesia due to the risk associated with the latter in pregnant women (such as difficult management of airway) [2]. However, neuraxial anaesthesia can also lead to adverse effects, in particular, post-dural puncture headache (PDPH). The incidence of PDPH following dural puncture mainly depends on the type of needle used (diameter, bevel) [3–10]. For instance, the incidence is reported to be between 0.7% and 4% when 24–27 G conical needles are used for spinal anaesthesia and between 50% and 85% when large Tuohy needles are used for epidural analgesia [3, 10, 11]. Since the incidence of dural puncture during epidural placement is reported to range from 0.04 to 6% [12], the incidence of PDPH among patients receiving these type of anaesthesia (spinal and epidural) is actually similar. In addition, postpartum women are more prone to PDPH than the general population [13–15].

PDPH is a clinical diagnosis. According to the International Headache Society, it is a severe postural, bilateral, disabling, constrictive, occipital or diffuse headache that radiates to the neck and develops within 7 days after the dural puncture. In 66% of cases, it occurs during the first 48 h, and in 90% of cases, during the first 3 days [3]. PDPH is aggravated by a sitting or standing position and is relieved by lying down. Other symptoms such as neck stiffness, hearing disorders (tinnitus, hypoacusia) [16], dizziness, photophobia, nausea or vomiting, and diplopia by injury of the cranial nerve IV [17] may be associated with the headache, and patients remain afebrile. Differential diagnoses are migraine, pre-eclampsia, meningitis, intracranial haemorrhage, cerebral thrombosis, pneumocephalus and tension headaches [18, 19].

As described by Vandam and Dripps, as early as 1956 [20], the main cause of PDPH appeared to be intracranial hypotension by leakage of cerebrospinal fluid (CSF). CSF is critical in reducing impacts between the brain and the cranium during orthostatism, and the loss of this cushioning leads to headaches. Furthermore, the cerebral and meningeal vessels are stressed by the downward displacement of the brain during orthostatism. This caudal traction activates the stretch-sensitive receptors of the trigeminal nerves (frontal headache), glosso-pharyngeal and vagus nerves (occipital headache) [11, 21, 22], and the first three cervical nerves (arm pain or neck pain) [23]. According to the Monro-Kellie theory, headaches may also be related to painful venous and arterial cerebral vasodilation, which compensates for decreased CSF volume [3, 21]. In the inner ear, hypotension of the perilymph also causes an imbalance between endolymph and perilymph itself, thereby leading to hearing impairment, tinnitus and/or vertigo [16, 24].

In most cases, dural puncture closes spontaneously without consequence. PDPH is reported to resolve in more than 50% of patients within 4 days, and in more than 70% within a week. However, headache may persist in a limited number of patients [3, 20]. PDPH can limit patients’ activity, increase the duration of hospital stay and use of care [25] and is particularly disabling during the postpartum period, when the mother has to take care of her child. It is therefore important to treat this syndrome. Epidural blood patch is currently the gold standard and most effective treatment for PDPH. However, the timing for this treatment remains uncertain. Some studies have suggested a greater risk of failure when administering an early blood patch, although no causal link could be established [26–28]. The diminished effectiveness in this case, could be explained by the severity of the CSF leak [28]. Conversely, administering a delayed blood patch could increase bed rest duration. A delay of 24 to 36 h between the onset of headaches and the completion of a blood patch seems reasonable. However, delaying the blood patch by more than 48 h is not recommended [29].

Historically, the reported success rate after the first blood patch is approximately 80% [28, 30]. Recently, however, efficacy has been found to be lower (32% at most) [27]. Moreover, it is an invasive procedure that may result in rare but serious complications such as spinal subdural hematoma [31] or permanent paraparesis and cauda equina syndrome [32]. It may also trigger anxiety and discomfort in patients and can sometimes be painful (back pain, transient bradycardia).

Alternative treatments have recently been studied; they aim to be less invasive or to reduce headache intensity whilst waiting for the blood patch or the disappearance of PDPH. Several lines of evidence have suggested the effectiveness of adrenocorticotropic hormone (ACTH) in the management of PDPH [33–41]. Several mechanisms have been proposed to explain the effects of ACTH or its analogues on headaches. First, it has been shown by several teams that fragments of ACTH interact with opioid receptors *in vitro* and have morphine-like effects *in vivo* [42–44]. Second, ACTH may increase brain β-endorphins which can change the perception of pain [35–37]. Third, ACTH stimulates the adrenal cortex, which releases different hormones such as glucocorticoids, androgens and mineralocorticoids. Glucocorticoids have an anti-inflammatory effect that may explain in part the analgesia observed after ACTH injection [38]. Fourth, mineralocorticoids are responsible for fluid retention that may lead to meningeal oedema and overlapping edges of the dural puncture [36].

The trial reported by Hakim found that administration of tetracosactide after accidental dural puncture in 90 parturients was associated with a significant reduction in the incidence of PDPH and requirement for epidural blood patch [39]. The efficacy of tetracosactide for the treatment of PDPH in 32 patients has been reported to be 56% (95% CI [33; 79%]) [40], and to be similar to that of epidural blood patch in a study that included 28 patients [41], although 4 of the 15 in the tetracosactide group also received a blood patch. However, a randomized trial that included 18 patients did not find any efficacy of tetracosactide in the treatment of PDPH, nor in the reduction of blood patch use [45]. This study was conducted among a small group of patients and did not report any data on the interval between PDPH onset and blood patch. Taken together, efficacy evidence of ACTH analogues on PDPH remains limited, with contradictory results obtained in small groups of patients. Therefore, drawing conclusions and establishing a protocol for the management of PDPH are difficult.

In the proposed study, we have designed a therapeutic trial to evaluate the efficacy of tetracosactide in the treatment of PDPH in 88 postpartum patients.

## Methods/Design

### Aim of the study

The aim of this study is to assess the efficacy and safety of tetracosactide (Synacthen®) in the treatment of post-dural puncture syndrome for patients who received neuraxial anaesthesia during childbirth.

Our working hypothesis is that a single intravenous infusion of tetracosactide may avoid the need for the epidural blood patch. To challenge this hypothesis two groups will be compared: the study group receiving an infusion of 1 mg of tetracosactide and the control group receiving a placebo (0.9% saline). Both groups receive standard analgesic treatment and epidural blood patch if needed (after a minimum of 24 h following the injection of the experimental treatment).

### Trial design

The study is a randomised, double-blind, placebo-controlled, parallel-arm, double-centre trial. It is conducted in two different sites, and both sites are part of the same French university hospital. We followed the SPIRIT checklist (Additional file 1). Patient enrolment started in October 2016 and was expected to be completed within 2 years after the start of the study. However, as explained in section 1.3.11. this did not happen.

Once participants are enrolled in the study with informed consent, they are randomised into the two study arms. The study group receives 1 mg of tetracosactide intravenously whereas the control group receives 0.9% saline. Outcomes will be measured between 2 and 6 h, on day 1, day 2, day 3, and between days 13 and 17 post-randomisation. Adverse events are collected throughout the study.

### Primary endpoint

The primary endpoint of the study is the rate of epidural blood patch within a 15-day follow-up period, that is, the number of patients who receive a blood patch within the 15-day period divided by the total number of participants included.

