### Intervention protocols

During the post-partum period, patients are usually followed by midwives. In case of headache, whether an accidental dural puncture is diagnosed or not, the anaesthesiologist is informed by the midwives. Therefore, any symptomatic patient is examined by an anaesthesiologist. The study investigators are the anaesthesiologists working in the maternity department of the two centres.

Patients are enrolled when diagnosed with PDPH based on the anaesthesiologist’s clinical evaluation. They are randomised to receive intravenous tetracosactide or placebo. In the study group, patients receive a single intravenous injection of 1 mg tetracosactide (Synacthen®, Sigma-Tau laboratory, Roma, Italy). Four vials containing 0.25 mg tetracosactide (in 1 ml of solvent) are reconstituted in 100 ml of normal saline (0.9% NaCl). This solution is infused intravenously over 20 min. In the control group, patients receive an equal volume of normal saline: 104 ml over 20 min. The whole intervention is administered over a 20-min course and therefore is not modifiable once begun except for the occurrence of a side effect. A side effect is defined herein as any new abnormality observed upon clinical examination, occurring during the injection. In this case, the treatment is immediately stopped but monitoring and data collection continues.

Standard analgesic medication, as concomitant treatments, is also initiated in both groups from the beginning of headache, as follows:
for mild headache (NRS < 3/10): 1 g paracetamol and 400 mg ibuprofen orally every 6 hfor moderate headache (NRS = 3): nefopam 20 mg and/or a combination of paracetamol 300 mg and opium 10 mg is given in addition every 4 hfor severe headache (NRS ≥ 4): morphine 10 mg orally every 4 h can be added as required

These treatments are adjusted daily.

The primary and secondary endpoint, including tolerance criteria, are evaluated blinded during infusion of the study treatment, 2–6 h later, 1 day, 2 days, 3 days and between 13 and 17 days post-treatment by the investigator. The latter is conducted by phone call in order to increase the complete follow-up. The total duration of the study is therefore 13 to 17 days. Any alternative analgesic intervention required after receiving the study treatment is reported at each time point as indicated above. The study timeline is summarised in Fig. 2.

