### Statistical analysis

Unblinding occurs at the end of the study and once the database has been frozen. Analyses will be carried out on an intention-to-treat (ITT) basis. If data are missing from visits, we will carry forward the last value for which the pain (and other symptoms) has not improved. This is the most pessimistic scenario for this condition, which usually improves spontaneously. Blood patch can only be performed at the hospital, and it is therefore very unlikely that there will be missing data regarding the primary endpoint. If a patient does not receive full treatment, she will be included in the group to which she was randomised for further ITT analysis. Statistical analyses will be performed using IBM SPSS statistics for windows (IBM corp., Armonk, NY, USA) and R (R Foundation for Statistical Computing, Vienna, Austria). All data will be checked for normal distribution using the Kolmogorov test. For normally distributed data, variables will be presented as mean ± standard deviation (SD). Non-normally distributed data will be presented as the median and interquartile range [IQR]. Categorical variables will be presented as number and percentage of the total. To compare the two groups (tetracosactide and placebo), we will use Fisher’s exact test for qualitative data and the non-parametric Mann-Whitney tests for quantitative variables. A comparison of the two groups at randomisation will identify potential bias due to unequal allocation. A multivariate logistic regression analysis will be performed to study factors independently associated with the response to tetracosactide and to control potential confounding factors.

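### The final call can precede the end of the 15-day primary window, and a patch the trial never learns of counts as no patch: a small gap that is cheap to close

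*Protocol article*

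**What the plan says.** All of this is in the protocol article.

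- **Primary endpoint** defines the rate as "the number of patients who receive a blood patch within the 15-day period divided by the total number of participants included".
- **Intervention protocols** has the endpoints assessed during the infusion, 2–6 h later, and then "1 day, 2 days, 3 days and between 13 and 17 days post-treatment by the investigator". The last of these contacts is by phone. The section adds: "The total duration of the study is therefore 13 to 17 days". **Trial design** gives the same 13–17 day window.
- **Statistical analysis** states: "Analyses will be carried out on an intention-to-treat (ITT) basis". For missed visits, "we will carry forward the last value for which the pain (and other symptoms) has not improved", with the comment: "This is the most pessimistic scenario for this condition, which usually improves spontaneously". That rule is worded for pain and other symptoms and does not name the blood patch.
- On the primary endpoint itself, the same section says: "Blood patch can only be performed at the hospital, and it is therefore very unlikely that there will be missing data regarding the primary endpoint".

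**The concern.** Three features meet at the primary endpoint. The window runs to day 15, but the last contact may come one or two days earlier. After day 3 there is no other planned contact. And the ratio keeps every included woman in the denominator, so a patch that never becomes known is arithmetically the same as no patch.

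The argument that a patch needs a hospital says where it is done, not that this trial will hear of it. Trial design places both sites within one university hospital. A woman who has gone home could be patched elsewhere, or after a call made on day 13.

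At stake is the completeness of the primary outcome. Missed patches in both arms shrink the difference and cost power. Missed patches mainly on tetracosactide would flatter the drug; mainly on placebo, they would hide an effect.

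**Working it through.** **Inputs from the article.** 44 per group, p1 = 0.9, p2 = 0.6, Fisher's exact test, α = 0.025, power 0.80 (Number of patients needed); threshold p < 0.025 (Intermediate analysis). The article does not state sidedness; two-sided is used here.

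**Inputs assumed.** The article gives no loss rate and no distribution of patch times. Let *l* be the share of women lost after day 3 and *s* the share of patches that fall after day 3. Lost women are taken to be patched at the same rate as the rest of their arm, and every patch after day 3 in a lost woman is taken to be unseen.

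**Step 1: the plan's own figure.** Full enumeration of two binomials gives power 0.811 at 44 per group for 0.9 vs 0.6. The smallest n reaching 0.80 is 43. The planned size reproduces, with little to spare. With no effect at 0.9 vs 0.9, total type I error is 0.007.

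**Step 2: formula with unseen patches.** Observed rate = p × (1 − l × s).

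**Step 3: 10% loss, s = 10% to 30%.**
- l × s = 0.10 × 0.10 = 0.01 up to 0.10 × 0.30 = 0.03.
- Expected unseen patches in an arm with a 90% rate: 44 × 0.9 × 0.01 = 0.4 up to 44 × 0.9 × 0.03 = 1.2.

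| Scenario | Observed rates, placebo vs tetracosactide | Result |
|---|---|---|
| True 0.9 vs 0.6, loss in both arms, s = 10% | 0.891 vs 0.594 | power 0.79 |
| Same, s = 30% | 0.873 vs 0.582 | power 0.75 |
| True 0.9 vs 0.9, loss on tetracosactide only, s = 10% | 0.900 vs 0.891 | type I error 0.008 |
| Same, s = 30% | 0.900 vs 0.873 | type I error 0.013 |

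With 5% loss in both arms, power is 0.78–0.80.

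**Step 4: the extreme bound, s = 100%.** This treats all loss as coming before any patch.
- Power with equal loss: 0.71 at 5% and 0.62 at 10%.
- Type I error with loss on tetracosactide only: 0.023 at 5% and 0.081 at 10%.
- Type I error with equal 10% loss: 0.012.

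**Step 5: the early call alone.** Suppose 1–5% of patches fell on days 14–15 and were missed in every tetracosactide patient and in no control. Type I error would be 0.008–0.023, still below 0.025.

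**The case against.** The strongest reply is that the article considers missing primary data and judges them very unlikely, that its denominator is ordinary ITT, and that no sentence scores unknown status as success. A woman who is reached can report a patch done anywhere, since nothing restricts the call to the two sites. Detailed handling of the few remaining cases may sit in the full protocol or SAP. Most of this stands. It is why the point rests on what the article does fix (the ratio, the call window and the hospital argument) and not on an absent imputation rule.

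A reader might infer that every woman who withdraws, is lost or is called on day 13 counts as a success. The article does not support that: a woman patched before her last contact is in the numerator. Only a later patch that stays unknown is affected.

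A reader might also infer a real risk of a false positive, pointing to the 0.081 in step 4. That figure needs 10% loss on tetracosactide, none on placebo, and every lost woman's patch unseen. The trial is double-blind and nothing in the article suggests unequal loss. Patching is allowed from 24 h after study treatment and 36 h after the puncture, the Background advises against delay beyond 48 h, and contacts fall on days 1, 2 and 3. Most patches should therefore be observed directly.

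Nor does the pessimistic symptom rule contradict the primary endpoint, because the article treats the two separately.

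What remains is that a call on day 13 or 14 cannot confirm status through day 15, and that the hospital argument does not cover a patch at a non-study hospital.

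**Conclusion.** The point holds as a cheap improvement, not as a demonstrated source of bias. The follow-up schedule can end before the primary window does, and the ratio turns a patch that is never learned of into the favourable value.

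The more plausible harm is a modest loss of power, from 0.81 to about 0.75–0.79 with 10% loss in both arms. Type I error stays at or below about 0.013 even if that loss is confined to tetracosactide. Both ranges rest on an assumed 10–30% of patches after day 3 and an assumed 10% loss; the article gives neither figure. If loss is nil and every call falls on day 15 or later, nothing changes.

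**What to change.** 1. Make the final call on day 15–17 instead of day 13–17, and ask explicitly about patches at any hospital.
2. For women not reached or withdrawn, check the records of both sites, as consent allows.
3. Add one sensitivity analysis of the primary comparison in which status not confirmed through day 15 counts as patch received. Under no effect at 90%, with 10% loss in one arm only, that rule keeps type I error at 0.007.

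Imputation within arm as the primary analysis is not needed for an outcome expected to be almost complete.

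The cost is a call window two days shorter, one extra analysis and a few lines of wording. No additional patients or visits are required.

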### Secondary endpoints

The secondary endpoints are as follows:
duration of headache, that is, the mean number of days with headache within the 15-day follow-up periodintensity of headache (11-point numerical rating scale, NRS) [46], that is, the mean NRS at day 1, 2, 3, and 15the need for analgesic treatment (descriptive analysis of type, time interval after study treatment initiation, and duration) within the 15-day follow-up periodappearance of associated features (neck stiffness, tinnitus, hypoacusia, photophobia, diplopia, dizziness, or nausea), that is, a descriptive analysis of these features within the 15-day follow-up periodactivity limitation (self-assessed, both qualitatively as described in Fig. 1, and quantitatively on a scale from 0 to 100%), with a mean score give on days 1, 2, 3 and 15length of hospital stay, that is the mean number of days spent in hospital assessed from inclusion to day 15the number of epidural blood patches performed per patient, that is, the mean number within the 15-day follow-up periodtolerance, assessed by the collection of all adverse events (type, frequency, and severity)

**Fig. 1 Fig1:**
[figure not shown]
Questionnaire for qualitative assessment of activity limitation: a simple questionnaire corresponding to the needs of a postpartum patient

### Population

#### Number of patients needed

The sample size calculation is based on a previous study that investigated tetracosactide in PDPH [39] and, retrospectively, on observational data obtained from our hospital database. The primary endpoint is the rate of blood patch in the two groups. We defined the efficacy of tetracosactide as a decrease in blood patch use by 30% in the tetracosactide group, a clinically relevant difference reducing the need for invasive treatment and replacing it with an easily administered treatment that has a known safety profile.

In our centre, 90% of patients with PDPH after epidural analgesia receive a blood patch. The study reported by Hakim [39] found a greater than 50% decrease in PDPH incidence and blood patch use after prophylactic treatment with tetracosactide, in a context of epidural analgesia. We therefore need to include 44 subjects in each group, given a power of 0.80 and type I error of 0.025 (α = 2.5% Fisher’s exact test, power of 80%, p1 = 0.9; p2 = 0.6), to reduce the blood patch requirement by 30%. Thus a total of 88 patients need to be randomised.

